## Abstract

**Background:** Parkinson's disease (PD) is a progressive neurodegenerative disease with motor- and non-motor symptoms. When the disease progresses, symptom burden increases. Consequently, additional care demands develop, the complexity of treatment increases, and the patient's quality of life is progressively threatened. To address these challenges, there is growing awareness of the potential benefits of palliative care for people with PD. This includes communication about end-of-life issues, such as Advance Care Planning (ACP), which helps to elicit patient's needs and preferences on issues related to future treatment and care. In this study, we will assess the impact and feasibility of a nurse-led palliative care intervention for people with PD across diverse European care settings.

**Methods:** The intervention will be evaluated in a multicentre, open-label randomized controlled trial, with a parallel group design in seven European countries (Austria, Estonia, Germany, Greece, Italy, Sweden and United Kingdom). The “PD_Pal intervention” comprises (1) several consultations with a trained nurse who will perform ACP conversations and support care coordination and (2) use of a patient-directed “Parkinson Support Plan-workbook”. The primary endpoint is defined as the percentage of participants with documented ACP-decisions assessed at 6 months after baseline (t1). Secondary endpoints include patients' and family caregivers' quality of life, perceived care coordination, patients' symptom burden, and cost-effectiveness. In parallel, we will perform a process evaluation, to understand the feasibility of the intervention. Assessments are scheduled at baseline (t0), 6 months (t1), and 12 months (t2). Statistical analysis will be performed by means of Mantel–Haenszel methods and multilevel logistic regression models, correcting for multiple testing.

**Discussion:** This study will contribute to the current knowledge gap on the application of palliative care interventions for people with Parkinson's disease aimed at ameliorating quality of life and managing end-of-life perspectives. Studying the impact and feasibility of the intervention in seven European countries, each with their own cultural and organisational characteristics, will allow us to create a broad perspective on palliative care interventions for people with Parkinson's disease across settings.

**Clinical Trial Registration:**www.trialregister.nl, NL8180.

## Introduction

Parkinson's disease (PD) is the second most common neurodegenerative disease worldwide, affecting 1–2% of the world population above 65 years of age. The number of people with PD is expected to double from 6.9 million in 2015 to 14.2 million in 2040 (1). On average, people live for 15 years with the disease (2–4). As the disease progresses, people develop a range of motor as well as non-motor symptoms, which typically increase over time. For example, in a European cohort of 692 people diagnosed with late-stage PD and an average disease duration of 15 years, 68% reported off-periods for at least 50% of the day, 82% reported falls, and 92% experienced at least one neuropsychiatric symptom, with apathy, depression, and anxiety most commonly being present (5, 6). Furthermore, around 60% of patients with PD will ultimately develop dementia (7, 8). In light of this complex and multifaceted phenotype, it is understandable that treatment programs are complex, that quality of life becomes progressively threatened, and that informal carers experience considerable distress. However, despite the very high symptom burden at the end of life, end-of-life care in the field of PD often is not aligned with patients' needs and preferences (9, 10). Palliative care is often not introduced: in a cohort of advanced PD patients in Germany, with a mean disease duration of 17 years, 72% of the participants expressed an unmet need for palliative care (11). A large study including ~125,000 people with PD showed that 43% died in a hospital and only 9.7% in their homes, which is substantially lower compared to the 17% of the general elderly population dying at home. Hospice services were barely utilized, that is, in only 0.6% of the patients (12).

To address these challenges, there is growing awareness of the potential benefits of palliative care for people with PD (13, 14). According to the World Health Organization definition, published in 2012, palliative care is “an approach that improves the quality of life of patients and their families facing the problems associated with life threatening illness, through the prevention and relief of suffering by means of early identification and impeccable assessment and treatment of pain and other problems, physical, psychosocial and spiritual” (15). Advance Care Planning (ACP) is a cornerstone for palliative care, involving the timely identification and definition of goals as well as preferences for future medical treatment and care, discussion of these goals and preferences with family and healthcare providers, and recording and reviewing of these preferences if appropriate (16). There is a vast amount of international evidence, particularly in the field of oncology, on the benefits of palliative care in improving quality of life, increasing satisfaction with care and, for some patients, prolonging life (17–19).

Although the importance of palliative care for chronic neurological conditions has been well-established in the setting of clinical studies (13, 20, 21), in real life, many PD patients do not receive the support they need. Unlike conditions that are life-threatening immediately after diagnosis, the sense of urgency seems to be lacking in a slowly progressive and long-lasting condition like PD. The unpredictable prognosis makes it difficult to define a clear referral cutoff point, which prevents neurologists from appropriately referring patients to specialist palliative care services. Moreover, many physicians lack the communication skills and do not want to take away hope and patience (22). PD patients' acceptance of their symptoms as part of their everyday life, believing that no effective treatments are available, is an important barrier to report non-motor symptoms (23), hampering the recognition of palliative care needs.

Only recently, several studies have explored how palliative care principles should be designed and implemented to effectively support and treat people with PD (24–28). Foremost, effective palliative care requires an individualized approach, and patients should actively be invited to discuss ACP early on in the course of the disease and on a regular basis; palliative care requires skilled professionals who are knowledgeable on both PD and palliative care, and ACP decisions should be clearly documented and shared with relevant services. Finally, given the multidisciplinary nature of palliative care, care coordination should be an explicit responsibility of the care team (24, 29, 30).

Further studies are needed to evaluate the positive effects of palliative care models across a range of healthcare systems. The current PD_Pal trial was designed to understand the impact of palliative care services for PD, within a wide range of European healthcare systems. An evidence-based intervention will be evaluated consisting of a nurse-led, person-centred palliative care model for people with PD living at home, assisted living situation, or nursing homes. The intervention deals with two major challenges that many people with PD encounter (31, 32):

Increasing risk of cognitive and/or communication impairments that hinder the ability to easily discuss or indicate preferences about healthcare and quality of life when the disease advances. Therefore, timely documentation of patients' wishes related to advanced and end-of-life care is essential, but rarely part of standard care.The lack of care coordination during the transition from clinic-based care (focused on adjusting patients' medical treatment to control symptoms) to community-based care (focused on adjusting patients' care and daily living routines to comfortably live with the symptoms that can no longer be completely controlled).

The objective of this study is two-fold. First, we will determine the effectiveness of a nurse-led, person-centred palliative care intervention for people with PD and their family caregivers compared to care as usual. To evaluate this intervention, we will primarily focus on ACP documentation in the medical files, to demonstrate that relevant end-of-life issues were indeed discussed. Additional outcomes will focus on patients' clinical outcomes, caregivers' quality of life, patients' and caregivers' costs and service utilisation. Second, we will assess the feasibility of the PD_Pal intervention across seven European countries (Austria, Estonia, Germany, Greece, Italy, Sweden and United Kingdom).

## Methods and Analysis

### Study Design

The intervention will be evaluated in a multicentre, single-blinded randomized controlled parallel group design, in seven European countries. Within each participating country, one trial centre will lead the recruitment. Participants will be randomized in a 1:1 ratio to either the intervention or the control group, who will receive care as usual. The intervention will be delivered during the first 6 months after randomisation. Assessments will be performed at baseline (t0), at the end of the intervention phase, that is, after 6 months (t1), and after 12 months (t2) for follow-up (see Figure 1).

**Figure 1 F1:**
[figure not shown]
Study flowchart of the PD_Pal clinical trial.

Participating clinical centres should have at least one movement disorder specialist available. Centres are excluded if they already apply a palliative care model as part of their routine care workflow; if they have detailed palliative care guidelines available with corresponding high-quality practices; and/or if the centre is participating or has participated in a palliative care study in the past 3 years.

### Study Population

The intervention targets individuals diagnosed with idiopathic PD or an atypical parkinsonism syndrome, independent of their age.

In order to be eligible to participate in this study, a person should meet all of the following criteria:

Meeting the clinical diagnostic criteria for PD, as defined by the Movement Disorders Society (33), or the criteria for an atypical parkinsonism syndrome (34);Hoehn & Yahr ≥3 (35);Progressive deterioration in physical and/or cognitive function despite optimal therapy, according to the primary physician;Cognitively able to complete questionnaires and to participate in interviews;Ability to provide written informed consent; andAvailability of a family caregiver or informal caregiver, jointly abbreviated as “FC” in the remainder of this article.

Furthermore, persons are excluded from participation if one of the following criteria are met:

Inability to communicate independently, with or without supportive communication tools;Unable or unwilling to commit to study procedures;Presence of additional chronic medical illnesses which may require palliative services (e.g., metastatic cancer);Already receiving palliative care or hospice services; and/orAlready participating in a clinical study for palliative care.

Having a device-assistant advanced treatment [including deep brain stimulation (DBS), levodopa–carbidopa intestinal gel (LCIG), and continuous subcutaneous apomorphine infusion (CSAI)], or considering one, is not an exclusion criterion. We will identify patients who certainly have complex medical needs and at the same time are still able to commit to ACP conversations and make decision.

The participation of a FC is compulsory. The FC should meet the following criteria:

Willing to provide written informed consent;Cognitively able to complete questionnaires and to participate in interviews;Aging ≥ 18 years; andIdentified by the person with PD as the FC.

### Sample Size Calculation

We assume that 5% of the target population will have documented ACP wishes at baseline. The study is powered to show a 20% absolute increase from a baseline of 5% (control group) in the primary outcome measure, that is, documented ACP-decisions, at 6 months, with a power of 0.80, a statistical significance of 0.05 (two sided) and an intraclass correlation coefficient (correcting for clustering within countries) of 0.10, by a Fisher's exact test. With the above assumptions, 74 patients in each treatment group are required. The sample size will be increased to 93 patients in each treatment group for allowing a 25% dropout rate within the 6-month follow-up period for the primary outcome effectiveness evaluation.

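### The 74 per group does not follow from Fisher's exact test with a country ICC of 0.10, and an inflation for country-level clustering does not fit individual randomisation

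*Protocol article*

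**What the plan says.** All from the protocol article.

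- Sample Size Calculation, effect: "The study is powered to show a 20% absolute increase from a baseline of 5% (control group) in the primary outcome measure", that is, 5% versus 25% with documented ACP decisions at 6 months.
- Same section, error rates and test: "with a power of 0.80, a statistical significance of 0.05 (two sided"), and the calculation is made "by a Fisher's exact test".
- Same section, clustering: "an intraclass correlation coefficient (correcting for clustering within countries) of 0.10". No cluster size or design effect is given.
- Same section, result: "With the above assumptions, 74 patients in each treatment group are required". This is then raised to 93 per group for 25% dropout.
- Study Design: seven countries, one lead centre in each, and "Participants will be randomized in a 1:1 ratio to either the intervention or the control group". The randomisation section confirms that the unit is the individual patient, allocated after the baseline visit.
- Statistical Analysis, Primary Endpoint: a Mantel-Haenszel method and a multilevel logistic model with country as the cluster.

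**The concern.** The section gives inputs, test and result together and presents the result as their consequence, so a reader should be able to recover 74 from them. If that fails, the stated 80% is not the power of the design. Neither the number of losses the trial can bear nor the meaning of a null result can then be read from it.

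There is also a question of fit. The inflation 1 + (m − 1) × ICC is made for trials that allocate whole clusters. Here both arms are expected within every country, and the analysis compares them there.

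**Working it through.** **Inputs.** Control rate 5%, intervention rate 25%, two-sided alpha 0.05, power 0.80, Fisher's exact test, ICC 0.10, 74 per group, 25% dropout and 93 per group (Sample Size Calculation). Seven countries and individual 1:1 allocation (Study Design).

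**Step 1: Fisher's exact test without the ICC.** Power is the summed probability of all pairs of binomial outcomes for which the two-sided exact p-value is at most 0.05.

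| n per group | Power |
|---|---|
| 54 | 0.791 |
| 55 | 0.801 |
| 69 | 0.903 |
| 70 | 0.908 |
| 74 | 0.924 |

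The requirement is 55, not 74. Other two-sided formulas without the ICC also miss 74: pooled z 49, continuity-corrected 59, unpooled z 47, arcsine 45.

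**Step 2: add the ICC over seven countries.** The design effect is DE = 1 + (m − 1) × 0.10, starting from 55.

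- Cluster size per arm, one pass: m = 55/7 = 7.86, DE = 1.686, n = 55 × 1.686 = 92.7, so 93.
- Cluster size over both arms, one pass: m = 110/7 = 15.71, DE = 2.471, n = 135.9, so 136.
- Per-arm cluster size matched to the final n: n = 55 × (0.9 + 0.1n/7). Hence n × (1 − 5.5/7) = 49.5 and n = 231.
- Both-arm cluster size matched to the final n: the factor is 1 − 11/7, which is negative, so there is no finite solution.

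The 93 in the first line coincides with the protocol's 93 only by chance. The protocol obtains 93 from dropout: 74 × 1.25 = 92.5.

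**Step 3: what would produce 74.** From 55, DE must be 74/55 = 1.345, so m = 1 + 0.345/0.10 = 4.45. But 74 per arm over seven countries is 74/7 = 10.6.

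The unpooled z formula does get there: (1.960 + 0.842)² × (0.05 × 0.95 + 0.25 × 0.75)/0.20² = 46.1, so 47. With m = 47/7 = 6.71, DE = 1.571, and 47 × 1.571 = 73.9. This route is not Fisher's test, and its cluster size of 6.7 does not match the 10.6 implied by 74 per arm.

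**Step 4: power under the actual design.** A Mantel-Haenszel test stratified by country was simulated with seven equal countries. Where country rates vary, they were assumed beta-distributed with ICC 0.10; this is an assumption, since the protocol gives no distribution.

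| Country variation | 74 per group | 70 per group |
|---|---|---|
| None | 0.952 | 0.942 |
| Same ranking of countries in both arms | 0.968 | 0.959 |
| Independent in the two arms | 0.888 | 0.883 |

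Variation shared by the arms does not lower the power. Variation that differs between arms, which is variation of the treatment effect, does.

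**Step 5: after dropout.** 93 × 0.75 = 69.75, so about 70 per group. Fisher power there is 0.903 (at 69) to 0.908 (at 70).

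**The case against.** - **The article is condensed.** The full protocol may show the cluster size and formula. That excuses the missing working. It does not excuse a sentence whose test, ICC, power and result disagree with one another.
- **74 can be reached.** A reader might infer that no calculation at all yields 74. That goes too far: the unpooled z route in step 3 does, and it may be the source. What stands is that 74 does not follow from the test the section names.
- **Some allowance may be sensible.** A reader might infer that no inflation could ever be justified here. The documents do not support that. The Control Group section expects usual care, and the ACP within it, to differ by country. The workbook is adapted nationally, and delivery is tailored to patient and caregiver. A treatment effect that varies by country or nurse is plausible and does not cancel within strata. But the ICC is described as clustering within countries, not as variation of the effect.
- **Stratified randomisation by country is not stated.** True. The argument rests on individual allocation, which puts both arms in each country in expectation, together with the country-based analysis.
- **Is the trial underpowered?** A reader who applies the design effect literally at 74 per group gets DE of 1.96 or 3.01, an effective 38 or 25 per arm, and power between about 0.37 and 0.61. Those figures come from a cluster-randomisation formula and do not describe this trial.

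**Conclusion.** The point holds as a should-fix. As written, 74 per group at 80% power is not a consequence of Fisher's exact test with a country ICC of 0.10: the same inputs give 55 without the ICC, and 93 or 136 with it in one pass. A design effect for outcome level shared within a country does not belong in an individually randomised trial analysed by country.

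With countries treated as strata, the error is conservative: Fisher power is about 92% at 74 and about 91% at 70, against the 80% claimed. This rests on the protocol's own 5% and 25%.

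The 89% for rates varying independently by arm rests in addition on the beta assumption, seven equal countries and a Mantel-Haenszel test that treats countries as fixed strata. An analysis with a random treatment effect by country would have lower power. No figure is claimed for that here.

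**What to change.** Restate the Sample Size Calculation paragraph so that test, ICC and power agree.

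1. Remove the country-level design effect. State that 55 evaluable patients per group give 80% power by Fisher's exact test, that 74 give about 92%, and that the roughly 70 left after 25% dropout from 93 give about 91%, with country as a stratum in the analysis.
2. If an allowance for a treatment effect that varies by country or nurse was intended, say so. Give the number and size of those clusters and the power under that structure. For orientation, it is about 89% at 74 per group in the simulation with country rates independent by arm and ICC 0.10.

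The cost is the rewording of one paragraph, plus a short power calculation if the second option applies. Recruitment need not change.

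### Dropout allowance: 93 per group is 74 × 1.25, which leaves about 70 evaluable at 25% dropout, not the 74 required

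*Protocol article*

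**What the plan says.** The statements are all in the Sample Size Calculation section of the protocol article. The target is set by the primary outcome: "The study is powered to show a 20% absolute increase from a baseline of 5% (control group) in the primary outcome measure", with 80% power at a two-sided 5% level and "an intraclass correlation coefficient (correcting for clustering within countries) of 0.10, by a Fisher's exact test". The result is given as "With the above assumptions, 74 patients in each treatment group are required". The next sentence adds the allowance for loss: "The sample size will be increased to 93 patients in each treatment group for allowing a 25% dropout rate within the 6-month follow-up period". That sentence goes on to tie the allowance to the evaluation of the primary outcome. The inflation formula is not given. Allocation is 1:1 (Study Design), so the planned total is 2 × 93 = 186.

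**The concern.** The two sample-size figures and the dropout rate do not fit together. A dropout rate is ordinarily a proportion of the patients randomised. If so, the number to randomise is the required number divided by one minus the rate. Multiplying by one plus the rate always gives too few, and the gap widens as the rate rises; at 25% it is no longer a matter of rounding.

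At stake is the recruitment target for the primary endpoint. The natural reading of the section is that the trial keeps its 80% power if a quarter of patients are lost by 6 months. If the allowance is too small, the trial falls below its own required number in exactly the situation the allowance was meant to cover.

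**Working it through.** **Inputs** (all from Sample Size Calculation): 74 required per group; 25% dropout by 6 months; 93 per group after the allowance; power 0.80; two-sided alpha 0.05; ICC 0.10. Seven countries, from Study Design.

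**Reproducing the plan's figure**

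- Multiplying: 74 × (1 + 0.25) = 92.5, rounded up to **93**. This matches exactly.
- Dividing: 74 / (1 − 0.25) = 98.67, rounded up to **99**. This does not match.

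So 93 was almost certainly obtained by multiplying.

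**What 93 delivers**

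- Evaluable at 25% dropout: 93 × 0.75 = 69.75, about 70 per group. The shortfall is 74 − 69.75 = 4.25 per group, or 4.25/74 = 5.7%.
- Largest dropout that still leaves 74: 1 − 74/93 = 0.204, or 20.4%.
- Check at 20%: 93 × 0.80 = 74.4, which is sufficient.
- Gap in the number randomised: 99 − 93 = 6 per group, 12 in total (198 against 186).

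**Effect on power, taking as given that 74 yields 0.80**

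With a normal approximation and information proportional to the number of patients:

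- Power = Φ[(1.960 + 0.842) × √(69.75/74) − 1.960] = Φ(0.760) = **0.776**.

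The section says that 74 already allows for clustering within countries but does not say how. If a conventional design effect 1 + (m − 1) × 0.10 was used (my assumption), losing patients also shrinks the cluster size m, so effective information falls by less than 5.7%:

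- m counted per arm: m goes from 74/7 = 10.57 to 69.75/7 = 9.96, and the design effect from 1.957 to 1.896. Effective-size ratio = (69.75/1.896)/(74/1.957) = 0.973. Power = Φ(2.802 × √0.973 − 1.960) = **0.789**.
- m counted over both arms: m goes from 148/7 = 21.14 to 139.5/7 = 19.93, and the design effect from 3.014 to 2.893. Ratio = 0.982. Power = Φ(2.802 × √0.982 − 1.960) = **0.793**.

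On the protocol's own premise, power after 25% dropout is therefore about 0.78 to 0.79.

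**Limit of the power figures**

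The 74 could not be reproduced from the stated inputs. Without clustering, Fisher's exact test for 5% against 25% reaches 0.801 at 55 per group, and has power 0.908 at 70 and 0.924 at 74. With the design effect above (m per arm), the simplest unclustered size of 49 per group (normal approximation, no continuity correction) becomes 49 × 1.957 = 95.9, already above 74. The shortfall against 74 does not depend on this; the power consequence does.

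**The case against.** The arithmetic is hard to dispute, so the case on the other side concerns how much it matters.

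- *The power loss is small and uncertain.* This stands. It is 1 to 2.5 percentage points if 74 gives 0.80. Because the origin of 74 is unclear, the real power at 70 is not known; without clustering it would be well above 0.80. But the protocol declares an ICC of 0.10 and states 74 as the requirement, so it cannot also rely on slack that exists only if clustering is ignored.
- *Loss on this endpoint may be below 25%.* The endpoint is read from medical records by chart review (Table 2) and analysed by intention to treat (Statistical Analysis), so a patient who stops attending may still contribute. That is plausible, but the section applies the 25% to the primary outcome evaluation itself. If less loss is expected, the stated rate should be lower.
- *The 25% could be meant relative to completers.* The formula is not stated, so this reading cannot be excluded. It would equal a loss of about 20% of those randomised, which is the restatement recommended here.
- *The 74 might already include dropout.* Numerically, 55/0.75 = 73.3 rounds up to 74. But the text gives 74 as the requirement and introduces dropout only afterwards, so this is conjecture.
- *The 80% power after dropout is inferred.* True: 0.80 is attached to 74, and 93 is described only as allowing for dropout. An allowance that does not restore the required number has no other evident purpose, so the inference is fair.

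**Conclusion.** The figure is wrong as written. With 25% of patients lost, 93 per group leaves about 70 evaluable, roughly 4 (6%) below the 74 that the preceding sentence requires. It supports 74 only up to 20.4% dropout; 25% would need 99 per group. This rests on three stated numbers (74, 25% and 93) and on reading dropout as a proportion of those randomised.

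The consequence is modest: power of about 0.78 to 0.79 instead of 0.80, conditional on 74 giving 0.80, with the upper part of that range also resting on an assumed design effect. Type I error, the endpoint and the analysis are unaffected. It should still be corrected, because it is the stated basis for the recruitment target on the primary endpoint and the error can be confirmed by hand.

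**What to change.** Correct the dropout sentence in Sample Size Calculation in one of these ways:

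1. Keep 93 per group and say that it allows for about 20% dropout by 6 months (93 × 0.80 = 74.4).
2. Keep 93 and 25%, state that about 70 per group are expected to be evaluable, and give the power at 70 by the same method that produced 74.
3. Keep 25% and 74 evaluable, and raise the target to 99 per group (198 in total).

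The first two cost one sentence and a slightly less favourable planning figure, with no extra recruitment. The third costs 12 more patients. Whichever is chosen, state that the dropout rate is a proportion of those randomised and show the division.
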